### Data collection

Data will be collected at three time points: baseline, 3 months post-intervention, and 6 months post-intervention. All data will be collected through app-based online surveys and will be stored in the backend database of app with password limiting the access. If caregivers fail to complete app-based surveys, we will provide printed paper questionnaires to participants through the support of facilitating teachers. In addition, an independent app-based survey among a sample of 100 caregivers will be conducted at each time period to test the reproducibility of collected data.

We also will collect compliance data through electronic strategies embedded in the app. These will include frequency of login, length of time using the app at each log-in, the number of knowledge disseminations used and listed as bookmarks, the number of published comments, and so on.

### Data analysis plan

Analysis will follow the intention-to-treat approach [38]. Descriptive data (mean, standard deviation, median, inter-quartile range, proportion) will be calculated to describe the characteristics of primary and secondary outcome measures and covariates. Chi-square test (categorical outcomes) and two sample independent *t*-test (continuous outcomes) will examine differences in unintentional injury incidence and other outcome indicators between the two arms at each time point (baseline, 3 months, 6 months). Chi-square test (categorical outcomes) and analysis of variance for repeated measurement data (continuous outcomes) will detect differences across the three time points for each arm.

The primary analysis will be conducted through Generalized Estimation Equation (GEE) models, which will test the effectiveness of the app-based intervention based on the interaction of group (intervention vs. control) with time (baseline, 3 months, 6 months) after adjusting for socio-demographic variables (age, sex, household income) and compliance to the intervention (use of the app-based interventions).

Missing values will be imputed using the Expectation Maximization algorithm (EM). To test the robustness of results, sensitivity analysis will be conducted by comparing primary and secondary outcome data collected through the online app-based survey and those completed using a printed questionnaire survey. Statistical analysis will be performed through Stata/IC 12.1. Statistical significance will be based on 2-sided tests at the level of 0.05.

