****Method**:**

A single-blinded, 6-month, parallel-group cluster randomized controlled trial with 1:1 allocation ratio will be conducted in Changsha, China. In total, 2626 caregivers of preschoolers ages 3–6 years old who own a smartphone will be recruited from 20 preschools. Clusters will be randomized at the preschool level and allocated to either the control group (routine education plus app-based parenting education excluding unintentional injury prevention) or the intervention group (routine education plus app-based parenting education including unintentional injury prevention). The app-based injury prevention program was developed based on the Theory of Planned Behavior, the Haddon Matrix, the Mobile Learning framework, and a needs assessment. Data collection will be conducted at baseline, 3-month, and 6-month follow-up via app-based survey plus printed questionnaire survey. The primary outcome measure is unintentional injury incidence among preschoolers in the past 3 months. Secondary outcome measures include economic losses due to unintentional injury in the past 3 months, the Incremental Cost-Effectiveness Ratios (ICERs), and parent’s attitudes and behaviors concerning supervision to prevent preschooler unintentional injury in the past week. An intention-to-treat approach will be used to evaluate outcome measures. Chi-square tests will examine differences for outcome measures between groups at each time point and generalized estimation equations (GEE) will test the overall effectiveness of the app-based intervention. Missing outcome data will be imputed using the Expectation Maximization algorithm (EM).

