### Secondary outcome measures

We will collect data on several secondary outcomes measures, as detailed below.Caregiver attitudes toward unintentional injury prevention and safety behaviors among preschoolers will be assessed through a 17-item questionnaire. Items will focus on attitudes over the past week; the instrument was validated in previous epidemiological studies and is considered reliable and valid [34, 35]. Two items focus on caregivers’ attitudes for unintentional injury prevention and are assessed using a 4-point scale (completely, partly, not at all, don’t know): (a) Do you think child unintentional injury is largely preventable? and (b) Do you think you can help keep your child free from unintentional injuries? The remaining fifteen items assess caregiver report on the frequency of child’s risky behaviors over the past week, both indoors and outdoors (e.g., leave the child alone in the bathtub; require the child to use a helmet, wrist guard and other protective equipment when riding a bicycle, e-bike, or motorcycle).Caregiver report on economic losses due to unintentional injury will be measured through a 5-item questionnaire that assesses both direct economic costs caused by unintentional injury (medical treatment expenses; transportation expenses to and from hospital/clinic; payment to hire other persons to take care of the injured child; accommodation expenses for the caregivers who look after hospitalized children) and indirect economic costs that are the consequence of unintentional injury events (e.g., caregiver economic loss from being off work).We will also consider the Incremental Cost-Effectiveness Ratios (ICERs) for the app-based unintentional injury intervention. Cost-effectiveness analysis of the app-based unintentional injury intervention will follow National Institute for Health and Clinical Excellence (NICE) guidance on cost-effectiveness evaluation of public health interventions [36]. We will collect data on capital and time costs. Economic costs will consist of subsidies to the researchers and teachers paid by this project, costs for developing and maintaining the app-based interventions, and costs for efforts to increase compliance to using the app-based interventions Caregiver’s time costs will be collected retrospectively for the 6-month follow-up. Because many caregivers may be reluctant or untruthful in reporting their exact wages (individual incomes are regarded as highly private information by many adults in China), we will use the average salary in Changsha, China to calculate the product of total lost months due to taking care of the injured children to estimate the indirect economic loss for adult caregivers because of being off work.

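### If the fifteen behaviour-frequency items are analysed as categories, the planned between-arm chi-square test ignores their order and loses power at modest effects

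*Protocol article*

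**What the plan says.** The Data analysis plan assigns "Chi-square test (categorical outcomes) and two sample independent" t-tests (continuous outcomes) to the comparisons of arms. These tests "will examine differences in unintentional injury incidence and other outcome indicators between the two arms at each time point". The Abstract's Method paragraph is shorter: "Chi-square tests will examine differences for outcome measures between groups at each time point". Neither place names a test for ordered data.

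Secondary outcome measures describes a 17-item questionnaire. Two attitude items use a "4-point scale (completely, partly, not at all, don’t know" response set. "The remaining fifteen items assess caregiver report on the frequency of" risky behaviours in the past week. The article does not give the answer levels of these fifteen items, or say whether they are analysed singly, summed into a score, or kept as categories.

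The per-time-point tests are not the main analysis: "The primary analysis will be conducted through Generalized Estimation Equation (GEE) models", based on the group-by-time interaction.

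**The concern.** The objective for caregiver behaviour is directional: the app should make caregivers safer, and behaviour is the route by which injuries are meant to fall. Answers on how often something happened have a natural order. A Pearson chi-square test gives the same p-value however the categories are rearranged, and spreads a one-directional shift over K − 1 degrees of freedom. If the frequency items go to that test, a modest real improvement is less likely to be detected at a given visit. A significant result may also reflect movement between categories that is not an improvement. This is separate from clustering: a chi-square test corrected for preschool would still ignore the order.

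**Working it through.** **Plan's own figure.** There is none for these items. The stated 1181 per arm is for the injury outcome and is used here only as the number analysed. Both tests below use the same n, so the comparison does not depend on how 1181 was derived.

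**Inputs from the protocol.** 1181 per arm; ICC 0.005; preschool size 140; 10 preschools per arm; two-sided 0.05.

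**Assumptions, not in the protocol.** Three to five ordered levels, the distributions shown below, a uniform (proportional-odds) shift, and clustering handled equally in both tests through an effective n.

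**Effective n per arm.**
- Preschool size 140: design effect 1 + 139 × 0.005 = 1.695; 1181 / 1.695 = 697.
- About 118 analysed per preschool (1181 / 10): 1 + 117 × 0.005 = 1.585; 1181 / 1.585 = 745.

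**Formulas.** Let p and q be the level probabilities in the two arms.
- Unordered test: λ = n Σ (pᵢ − qᵢ)² / (pᵢ + qᵢ), K − 1 df.
- Ordered test: λ = n [Σ sᵢ(pᵢ − qᵢ)]² / (2 Var(s)), 1 df, where s is the mid-rank (ridit) score and Var(s) is taken over the average of p and q.
- Power comes from the noncentral chi-square distribution.

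**One case in full.** Four equal levels, odds ratio 1.3, n = 697. The cumulative proportions 0.25, 0.50, 0.75 become 0.302, 0.565, 0.796, so q = 0.302, 0.263, 0.231, 0.204. Both noncentralities are about 7.46. The unordered test spends this on 3 df (power 62%), the ordered test on 1 df (78%). The gap comes from the degrees of freedom.

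**Power at n = 697, unordered v ordered (loss in points).**

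| Levels (%) | OR 1.2 | OR 1.3 | OR 1.4 | OR 1.5 |
|---|---|---|---|---|
| 3: 50/40/10 | 34 v 43 (9) | 62 v 73 (10) | 85 v 91 (6) | 95 v 98 (2) |
| 3: 70/25/5 | 28 v 36 (8) | 54 v 64 (11) | 77 v 85 (8) | 91 v 95 (4) |
| 4: equal | 33 v 48 (15) | 62 v 78 (16) | 85 v 94 (9) | 96 v 99 (3) |
| 4: 70/20/7/3 | 24 v 36 (12) | 48 v 65 (17) | 72 v 86 (14) | 88 v 96 (7) |
| 5: equal | 30 v 49 (19) | 58 v 79 (21) | 82 v 94 (12) | 95 v 99 (5) |

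Losses are computed before rounding. At OR 2.0 both tests have essentially 100% power and the loss is nil.

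The heavily skewed four-level item is the exception to the narrower ranges at 1.4 and 1.5. Its table row has the shift moving away from the common level. With the shift towards that level, the same formulas give 64% v 80% at OR 1.4 and 81% v 92% at OR 1.5, losses of about 16 and 11 points.

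**At n = 745 and OR 1.3.** Five levels (10/20/30/25/15%): 61% v 81%. Four equal levels: 65% v 81%. Three levels (10/45/45%): 65% v 75%.

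**As sample size.** The noncentrality needed for 80% power is 7.85 (1 df), 9.63 (2 df), 10.90 (3 df) and 11.94 (4 df). The ratios to 7.85 are 1.23, 1.39 and 1.52. For the same noncentrality per caregiver, the unordered test therefore needs about 23%, 39% or 52% more caregivers.

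**The case against.** The strongest objection is that the protocol never sends the fifteen items to the chi-square test. They belong to a questionnaire that may be scored, and scored items would go to the t-test, which is signed and has one degree of freedom. In the five-level and four-equal-level cases at n = 745 and OR 1.3, a t-test on equally spaced scores has 81% power in both, so nothing is lost. This stands. Scoring is a detail that an article may leave to the full plan, and its absence is not the finding. The point is therefore conditional on the items being kept as categories, a reading that the Abstract's mention of chi-square alone makes reasonable.

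A reader might infer three stronger points that the documents do not support.

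- *All seventeen items are ordered.* The two attitude items are not fully ordered, because the don't-know answer has no place in the grading. A chi-square test on that scale is defensible. Assume the other answers split 50/40/10 and n = 697. If the app only moved caregivers out of don't-know (10% to 5%), the unordered test would have 86% power. A trend test would have 42% if it ranked don't-know last and 5% if it dropped it. Splitting the scale into completely versus the rest is not a dependable gain either. At n = 745 and OR 1.3, with 20% answering completely, 50% partly and 30% not at all, it has 56% power against 67% unordered. With 10% don't-know it has 50% against 55%.
- *The analysis would give no direction.* That is true of the test statistic but not of the report. Proportions and means are to be described, and the GEE model gives signed estimates, although the article does not state its form for ordered items.
- *A fixed loss of 10 to 20 points.* Levels, distributions and effect size are all assumed, and the loss runs from none to about 21 points.

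**Conclusion.** The concern holds in a conditional and minor form. If the frequency-of-behaviour items are analysed as categories, the named between-arm test ignores their order. The cost is roughly 10 to 20 points of power at odds ratios of 1.2 to 1.3 (8 to 21 across the cases tabulated). It is about 6 to 13 points at 1.4 and 2 to 5 at 1.5, with skewed items above those ranges, and nil at 2.0. These figures rest on three to five levels, a uniform shift and an effective n of about 700 to 745 per arm; the protocol fixes neither the levels nor the shift. If the items are scored for the t-test, the loss largely disappears. Neither the injury outcome nor the GEE test of overall effectiveness is affected.

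**What to change.** In the Data analysis plan, add that ordered frequency items kept as categories will be compared between arms by a one-degree-of-freedom ordinal method that accounts for preschool clustering. A cumulative-logit model is one example, reporting one odds ratio with a 95% CI per comparison. Keep chi-square for nominal variables. Do not impose an order on the attitude scale, and do not adopt the completely-versus-other split on grounds of power.

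The cost is wording only, with no new data or participants. The small downside is that a single odds ratio assumes a roughly uniform shift across levels. The test is still valid when there is no effect, but the summary is less apt if the shift is uneven.

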### School recruitment

This study plans to recruit participants from 20 preschools in Changsha, China, 10 public and 10 private (note: preschools enroll children ages 3–6 years in China) (Figs. 1 and 2). All schools in Changsha with more than 100 enrolled students will be regarded as eligible schools and will receive an official invitation letter along with related materials about this project. Each facility that agrees to participate will select one teacher to coordinate recruitment of study participants. To avoid unwanted contamination within the same preschool, we will randomly allocate to the intervention versus control group at the school level, stratifying by public/private, such that 10 preschools will be in the intervention group and 10 in the control group, with each group including 5 public preschools and 5 private preschools.

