### Sample size

Sample size was calculated based on our primary hypothesis, to detect a difference between the intervention and control groups in unintentional injury incidence among preschoolers in the prior 3 months. Previous studies reported an unintentional injury incidence of 25.5% among preschoolers in central China in the past 1 year [22] and an effect size of 0.64 between intervention and control groups [23]. Considering 1 year recall periods underestimate injury rates by 55 and 72% (most are minor injuries) compared with one-month recall periods [24, 25], and use of a strict operational definition that restricts injury events to those that cause activity restriction of 1 day or longer or are treated by a doctor or other medical professional substantially undercounts injury events (typically minor or moderate injuries) [26], we assume unintentional injury incidence among preschoolers in the past 3 months will be 23%. On the basis of a previous report [27], we estimate an intra-class correlation (ICC) of 0.005 within a preschool of 140 students. Predicting an incidence of 23% in the control group, an effect size of 0.75 between intervention and control groups, and an ICC of 0.005, α = 0.05, 1-ß = 0.80, a minimum sample size of 1181 caregivers is needed for each group. Conservatively estimating an attrition rate of 10% in the six-month follow-up study, we will require a recruited sample size of 1323 each group. In total, therefore, we will enroll 2626 participants. Since most preschools have far more than 100 students enrolled, 20 preschools are amply sufficient to recruit the needed sample size.

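### The supporting between-arm tests at each time point ignore preschool clustering; for injury incidence at the planned ICC of 0.005, a nominal 5% test rejects a true null about 12–13% of the time

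*Protocol article*

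**What the plan says.** The abstract states the unit of randomisation: "Clusters will be randomized at the preschool level". School recruitment gives the numbers, with schools allocated "such that 10 preschools will be in the intervention group and 10 in the control group", five public and five private in each arm. The Sample size section allows for clustering: "we estimate an intra-class correlation (ICC) of 0.005 within a preschool of 140 students".

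The Data analysis plan then names the between-arm tests. A chi-square test for categorical outcomes and an independent two-sample t-test for continuous ones "will examine differences in unintentional injury incidence and other outcome indicators between the two arms at each time point", meaning baseline, 3 months and 6 months. The abstract repeats the first part: "Chi-square tests will examine differences for outcome measures between groups at each time point". Neither place mentions an adjustment for preschool. The decision rule is "Statistical significance will be based on 2-sided tests at the level of 0.05".

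A separate sentence covers change over time within each arm: a chi-square test where the outcome is categorical and a repeated-measures ANOVA where it is continuous, over all three assessments.

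The next paragraph of the same section labels a GEE model, testing the group-by-time interaction, as the primary analysis. The Study design section also commits the trial, in general terms, to analysis in line with the cluster extension of CONSORT.

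**The concern.** Caregivers from the same preschool are not independent observations when the preschool is what was randomised. The ordinary chi-square and t-tests compute their standard errors as if they were. The Sample size section accepts that preschools differ by more than chance, so the plan uses one variance when it counts participants and a smaller one when it compares arms.

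At stake are the separate 3-month and 6-month comparisons. The primary outcome is collected at both of those times, and these are the tests named for comparing arms at each. The same tests also cover the other outcome indicators. Their p-values would stand beside the GEE result under the same 0.05 rule, but with a higher false-positive rate.

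**Working it through.** **Inputs.** ICC 0.005, stated cluster size 140, 1181 evaluable per group, 1323 recruited per group and 2626 in total (Sample size); 10 preschools per arm (School recruitment); two-sided 0.05 (Data analysis plan). The implied cluster sizes are 1181/10 = 118.1 evaluable, 2626/20 = 131.3 enrolled, and 140 as stated.

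**The plan's own figure.** I read the effect size of 0.75 as a risk ratio, which gives 23% against 17.25%. The standard two-proportion formula at 80% power then gives 763 per arm before clustering. With 140 per preschool, 763 × 1.695 = 1294 after rounding up, not 1181. With 118.1 per preschool, 763 × 1.5855 = 1210, which is within 3% of 1181. The mismatch does not affect this point, because the error rate below depends only on the ICC and the cluster size m, and the range used covers all three sizes.

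**Formulas.** Design effect: DE = 1 + (m − 1) × ICC. True size of an unadjusted 5% test: 2 × [1 − Φ(1.96/√DE)].

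**Injury incidence at ICC 0.005**

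| Caregivers per preschool | DE | 1.96/√DE | True size | Simulated chi-square |
|---|---|---|---|---|
| 118.1 | 1 + 117.1 × 0.005 = 1.5855 | 1.557 | 12.0% | 11.9% |
| 131.3 | 1 + 130.3 × 0.005 = 1.6515 | 1.525 | 12.7% | 12.7% |
| 140 | 1 + 139 × 0.005 = 1.695 | 1.505 | 13.2% | 13.3% |

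The simulation used 200,000 beta-binomial trials with 10 preschools per arm, incidence 23% and whole-number cluster sizes (118, 131, 140). With a continuity correction the rates were 11.2%, 11.9% and 12.3%. The unadjusted standard error is too small by 1 − 1/√DE, which is 21% to 23%.

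**Sensitivity to the ICC, 118.1 to 140 per preschool.** ICC 0.001: 6.4–6.6%. ICC 0.01: 18–20%. ICC 0.02: 28–31%.

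**Continuous outcomes.** If a continuous outcome also had an ICC of 0.005, the unadjusted t-test would reject 11.9%, 12.6% and 13.3% of the time at the three cluster sizes. That ICC is an assumption, because the article gives none for these outcomes.

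**Does the remedy work?** On the same simulated incidence data, without strata, a t-test on the 20 preschool proportions rejected a true null 5.0% of the time at all three cluster sizes.

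**Cost in width.** √1.585 = 1.26 and √1.695 = 1.30, so an interval that respects clustering is about 26–30% wider. A t-test on 20 summaries has 20 − 2 = 18 degrees of freedom and a critical value of 2.10. Since 2.10/1.96 = 1.07, the width ratio is 1.26 × 1.07 = 1.35 to 1.30 × 1.07 = 1.39, or about 35–40% wider.

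**The case against.** The strongest reply is that these are not the trial's main test. The Data analysis plan labels the GEE as primary, and the abstract gives GEE the test of overall effectiveness. This stands. A reader might infer from the 12–13% that the primary test has that error rate, but the article does not support that. It does not name the unit on which the GEE clusters, so the figure can be neither carried over to the GEE nor ruled out for it. That is a separate question.

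Second, 0.005 is a planning value for injury incidence. A reader might apply 12–13% to attitudes, behaviours and economic losses as well. No ICC is given for them, so only the direction of the error can be claimed there. This stands too.

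Third, the within-arm comparisons might be read as too optimistic in the same way. They should not be. Continuous outcomes already get a repeated-measures analysis. For categorical outcomes, the chi-square across time does treat repeated reports on the same children as independent, but ignoring a positive within-child correlation generally makes a test of change conservative. The 12–13% does not apply to it. The plan also does not claim that within-arm change shows an intervention effect.

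Fourth, the commitment to the cluster extension of CONSORT might be thought to cover the gap. It does not. It is general, while the tests are named specifically in two places, and they conflict with it. For the same reason this is not a detail left to a fuller analysis plan.

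**Conclusion.** The point holds for the between-arm chi-square and t-tests at each time point. For injury incidence they reject a true null about 12–13% of the time instead of 5%, provided the ICC is 0.005 and preschools contribute 118 to 140 caregivers each. The range is about 6.5% at ICC 0.001 to 18–20% at ICC 0.01. Equal cluster sizes are assumed; unequal sizes would raise the figure, and the public/private balance could lower it slightly. For the other outcomes the inflation is upward for any positive ICC, but its size is unknown.

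The affected tests support the primary analysis rather than constitute it, so this should be fixed but does not by itself undermine the primary test. The within-arm chi-square across time is a smaller, separate fault: it uses the wrong test for repeated reports, and the likely error is towards caution.

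**What to change.** In the Data analysis plan and the abstract, replace the between-arm chi-square and t-tests at each time point with one of the following:

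- contrasts between arms at each time point from a model with preschool as the cluster, with a small-sample correction because there are only 20 clusters; or
- a t-test on the 20 preschool-level summaries, stratified by public/private.

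Take any within-arm comparison over time for categorical outcomes from the same model, so that repeated reports on a child are treated as such.

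The change needs only new wording in the analysis plan, with no change to conduct or data collection. Any interval reported with these comparisons becomes about 26–30% wider from the design effect, or about 35–40% wider with preschool-level t-tests on about 18 degrees of freedom (slightly fewer once stratified). Most of that extra width is uncertainty that the trial's own ICC already implies; the rest is the price of having few preschools.

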### Participant recruitment

All primary caregivers of preschoolers from participating schools will be eligible to participate in the study. We will exclude caregivers who do not own smartphones. We will include any adult who serves as primary caregiver for preschoolers aged 3–6 years old; most participants are expected to be parents or grandparents, but other family members, friends of the family, and baby-sitters or nannies will be eligible [21]. One teacher will be recruited at each selected school to inform eligible caregivers about the study via existing school-family communication channels, including social media platforms (WeChat and QQ), school apps, printed hand-outs, and oral notification. Caregivers who agree to consider participation will be provided a leaflet with an invitation letter, an information sheet outlining the benefits and responsibilities of project participation, and instructions to download, install and use the app.

Upon downloading the app for the first time, participants will view an online informed consent. Consenting participants will then be asked to complete an online baseline survey that collects information on demographic characteristics, attitudes toward child injury prevention, supervision behaviors in the prior week, and occurrence and details (including related costs) about any unintentional injury to their child in the past 3 months.

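### The only follow-up tests expressly assigned to the secondary outcomes ignore the caregivers' own baseline answers, so available precision goes unused

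*Protocol article*

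**What the plan says.** The Data analysis plan assigns two kinds of between-arm analysis.

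- **Per-visit tests.** A chi-square test for categorical outcomes and a t-test for continuous ones "will examine differences in unintentional injury incidence and other outcome indicators between the two arms at each time point (baseline, 3 months, 6 months"). The Abstract repeats this: "Chi-square tests will examine differences for outcome measures between groups at each time point". Neither sentence mentions a baseline term.
- **GEE.** "The primary analysis will be conducted through Generalized Estimation Equation (GEE) models, which will test the effectiveness of the app-based intervention", and the test is "based on the interaction of group (intervention vs. control) with time (baseline, 3 months, 6 months"). No baseline value of the outcome is listed among the covariates; the model is fitted "after adjusting for socio-demographic variables (age, sex, household income) and compliance to the intervention (use of the app-based interventions"). The Abstract says that "generalized estimation equations (GEE) will test the overall effectiveness of the app-based intervention". Neither section limits the GEE to injury incidence, and neither says that it covers the secondary outcomes.

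The baseline data exist. Under Participant recruitment, consenting caregivers "complete an online baseline survey that collects information on demographic characteristics, attitudes toward child injury prevention, supervision behaviors in the prior week", and the same survey records injuries in the preceding three months with their costs. Attitudes, behaviors and economic losses are therefore all measured before follow-up begins. The two attitude items are "assessed using a 4-point scale", one category of which is don't know.

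**The concern.** A caregiver's earlier answer to an item is often among the best predictors of the later answer. A follow-up-only test leaves that information in the error term. With 10 preschools per arm, the arms will also differ somewhat at baseline by chance, and a raw follow-up comparison carries part of that difference.

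The Objectives section makes improved caregiver attitudes and behaviors an aim of the study, so the precision of these comparisons matters. If the GEE is the intended analysis instead, baseline enters only as a level of time. That handles imbalance but is not the most precise use of the data.

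**Working it through.** **The plan's own figure.** There is none to reproduce for this point. The Sample size section concerns the injury outcome only; no power, effect size or correlation is given for the secondary outcomes.

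**Inputs from the article.** 10 preschools per arm (School recruitment); 1181 caregivers per arm and ICC 0.005 (Sample size). This gives 1181/10 = 118.1 caregivers per preschool. Applying that ICC to the secondary outcomes is an assumption.

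**Assumed input.** r, the correlation between a caregiver's baseline and follow-up value, shown over a range. The formulas assume a linear outcome, equal variance at both visits, and the same correlation at caregiver and preschool level. For categorical items they are approximate.

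**Step 1: variance of the arm difference, relative to the raw follow-up test (= 1).**

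- Group-by-time (change-type) contrast: 2(1-r)
- Baseline-adjusted comparison: 1-r²
- Effective sample size gained over the raw test: 1/(1-r²)
- Power of a comparison that has 80% unadjusted: Φ(2.80/√(1-r²) - 1.96)

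| r | Raw | Change-type, 2(1-r) | Adjusted, 1-r² | Fall from raw | Effective n | Power from 80% |
|---|---|---|---|---|---|---|
| 0.1 | 1 | 1.80 | 0.99 | 1% | 1.01 | 80% |
| 0.2 | 1 | 1.60 | 0.96 | 4% | 1.04 | 82% |
| 0.3 | 1 | 1.40 | 0.91 | 9% | 1.10 | 84% |
| 0.5 | 1 | 1.00 | 0.75 | 25% | 1.33 | 90% |
| 0.6 | 1 | 0.80 | 0.64 | 36% | 1.56 | 94% |

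**Step 2: is adjustment ever worse?** Against the raw test, 1-r² ≤ 1 for every r. Against the change-type contrast, 2(1-r) - (1-r²) = (1-r)² ≥ 0. So adjustment is at least as precise as either. The change-type contrast is less precise than the raw test whenever r < 0.5.

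**Step 3: size of chance baseline imbalance.** The design effect is 1 + 117.1 × 0.005 = 1.586. The SE of the baseline arm difference is √(2 × 1.586/1181) = 0.052 SD, so the 95% range is about ±0.10 SD. At an assumed ICC of 0.02, the design effect is 3.342, the SE 0.075 SD and the range about ±0.15 SD. Only about r times the imbalance passes into a raw follow-up comparison: at r = 0.5 and ICC 0.005, about ±0.05 SD.

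**The case against.** The strongest reply is that the GEE already does the job. It is described as testing the app's effectiveness, it is not confined to injuries, and it includes baseline as a time level. The per-visit tests are also run at baseline, cover injury incidence as well, and stand between the descriptive statistics and the primary analysis, so they read like a per-visit summary. Much of this stands. A reader might infer that the raw tests decide the secondary outcomes and that chance imbalance therefore enters the trial's conclusions. The text does not establish that: if the GEE covers these outcomes, its contrast removes the baseline difference and only a precision loss remains. But the text does not assign the GEE to them either, and on both readings baseline adjustment is at least as precise. The GEE also adjusts for compliance, which is measured after allocation, so it is not a clean substitute.

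Three further inferences should be resisted.

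- **Bias.** Under randomization, chance imbalance is part of the sampling variance of the raw comparison. It is not a second harm on top of lost precision.
- **A large gain for every outcome.** At the assumed 23% three-month incidence, most economic losses would be zero, so r of 0.1-0.2 is plausible and the gain is only 1-4%. Gains above 1-r² require preschool means to be more stable over time than individual answers, which the documents do not show.
- **Power lost by ignoring order.** A 3-df chi-square has 65% power where a 1-df ordered test has 80%, but only in the worst case and with all four categories ranked. Don't know has no natural rank, and the response categories of the behavior items are not given.

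**Conclusion.** The point holds as one of efficiency. The only between-arm tests expressly assigned to the secondary outcomes at 3 and 6 months ignore baseline measures that the trial collects. If the GEE is also meant for them, it uses baseline less efficiently than covariate adjustment would. Under the assumptions stated with the calculation, the gain over the raw tests runs from negligible at r = 0.1 to about a third of the variance at r = 0.6. It is likely to be small for economic losses; the case is stronger for attitudes and behaviors. Nothing here invalidates the analysis or bears on the primary outcome. The failure of the per-visit tests to allow for preschool clustering is a separate and larger defect, which baseline adjustment alone would not repair.

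**What to change.** In the Data analysis plan, state that each 3- and 6-month comparison of attitudes, behaviors and economic losses is a regression of the follow-up value on arm, with the caregiver's own baseline value of that outcome as covariate and preschool as the cluster. State that this model decides the secondary outcomes, and keep the raw per-visit tests and tables as description. Align the Abstract.

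An ordinal model is optional. Use it only where the response categories are truly ordered and a fixed rule for don't know is written down beforehand.

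The cost is a change of wording, a little more programming, and a stated rule for missing baseline items that is consistent with the planned EM imputation. No new data are needed.
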